##### Alcohol

Alcohol consumption will be assessed using items from the GLF to provide a measure of units of alcohol per week and number of binge sessions per week (e.g., participants will be asked to indicate on which days they have drunk alcohol in the last 7 days and the type and amount of alcohol they drank on each of those days). The Alcohol Use Disorders Identification Test (AUDIT) [37] will also be used at the six-month follow-up to assess hazardous and harmful patterns of alcohol use at university.

##### Smoking

Items based on the HSE will be used to assess participants’ current smoking status and the typical number of cigarettes/amount of tobacco smoked.

#### Secondary outcome measures

**Social cognitive variables** Brief measures of social cognitive variables for each behavior will be constructed in line with current recommendations [16]. Measures of self-efficacy (e.g., “If I wanted, I could easily engage in regular exercise at university”), perceived control (e.g., “Whether or not I engage in regular exercise at university is under my control”) and intention (e.g., “I intend to engage in regular exercise at university”) will be taken at all time points. Measures of attitude (e.g., “Engaging in regular exercise at university would be… good/bad”), subjective norms (e.g., “Most people who are important to me think I should/should not engage in regular exercise at university) and planning (e.g., “To what extent do you have a detailed plan about how to engage in regular exercise at university?”) will be taken at the one and six month follow-ups.

##### Health status

The EQ-5D-3L [38] is a short, standardized measure of health status that assesses levels of severity (no problems/some or moderate problems/extreme problems) in five dimensions: mobility, self-care, usual activities, pain/discomfort and anxiety/depression. The measure provides a descriptive profile and a single index value for health status, and is recommended as the measure of health-related quality of life for health economic evaluations in the UK [39].

##### Recreational drug use

To estimate the prevalence of recreational drug use in the sample, respondents will be asked to indicate the number of “yes” answers (0 or 5, 1, 2, 3, 4) to five questions – four of which have a 50% population prevalence (e.g., odd or even date of birth) and one of which is on their use of recreational drugs. In this way it is possible to estimate the prevalence of recreational drug use in the sample without being able to identify whether individual participants do or not use recreational drugs. This way of asking about drug use has been shown to encourage accurate reporting of a behavior that is illegal and could be regarded as socially undesirable [40].

##### BMI

Participants will record their height and weight so that BMI can be calculated.

##### Health services usage

Self-report data on the use of the health service (e.g., GP visits, hospitalizations) will be gathered at the six-month follow-up to explore whether there are differences in healthcare resource use between the intervention and control arms.

##### Academic performance

Average exam marks and registration status (i.e., registered, transferred, withdrawn, leave of absence) will be used to assess academic performance at the end of each semester. These data will be gathered from university records (with the participants’ consent).

##### Use of university sports facilities

Data on use (membership, number of visits) of the university sports facilities will be collected from Sport Sheffield (with the participants’ consent).

##### Engagement with the digital intervention

Various measures of engagement with the intervention will be recorded such as the overall number of visits, the number and type of pages visited, the number of implementation intention plans completed.

##### Biochemical measures

A random sample of approximately 100 participants from each arm of the trial will be recruited by email to assess biochemical markers of health behavior when they start university and at six-month follow-up. At each time point, participants will provide a hair sample (3cm long) that will be liquefied and analyzed for biochemical markers of various health behaviors related to alcohol consumption, fruit and vegetable intake, cigarette smoking and recreational drug use. Following extraction procedures, markers of alcohol, vitamins and minerals and nicotine will be quantified using liquid chromatography with tandem mass spectrometric detection (LC-MS/MS). In addition, evidence for social drug use will be detected by screening for commonly used drugs and their metabolites. A 6430 triple quadruple mass spectrometer (Agilent Technologies UK) will be employed with a dynamic-multiple reaction monitoring-liquid chromatography mass spectrometry (DYN-MRM-LC-MS/MS) method. These participants will also have their height and weight measured to calculate BMI.

### Results

#### Sample size calculations

A previous Internet-based intervention study on alcohol use among US students [41] sent emails to all new freshmen at the start of the semester; 55% completed the baseline questionnaire, of whom 63% were followed-up at one month. For the proposed trial, we have assumed that 50% of participants will complete the baseline questionnaire, of whom 60% will be followed-up at six months, producing a total sample size of 1200 (i.e., 600 per arm of the trial). With 600 participants per arm, the trial will have at least 80% power to detect a small effect size of *d* = 0.20 [42] with a two tailed significance level of .0127 (the p value has been adjusted to allow for multiplicity in the co-primary endpoints). For the hair analysis, participants will be randomly sampled from each arm of the trial with a maximum of 100 per arm which will be sufficient to detect a small to medium effect size of *d* = 0.40 (alpha = .05, power =. 80) [42].

#### Analysis

Primary analyses will adopt an intention-to-treat approach (i.e., all participants randomized to the intervention group will be analyzed regardless of whether they actually accessed the intervention). This approach provides a more conservative estimate of the effectiveness of an intervention than comparing the control condition with those in the intervention group who engaged with the intervention rather than the full group [43]. The primary outcomes will be performance of the four health behaviors (i.e., fruit and vegetable intake, physical activity, alcohol consumption, smoking) at the six-month follow-up. The primary analysis will comprise a series of analyses of covariance (ANCOVAs) to assess the impact of the intervention on performance of the targeted health behaviors at six months, controlling for baseline health behavior scores. For smoking, the analysis will assess the proportion of smokers at six-month follow-up in each arm of the trial with appropriate adjustment of baseline smoking status using a logistic regression. Statistical significance will be declared if any of the primary endpoints are significant at .0127. The analysis will be repeated for the same endpoints at one month as a secondary analysis.

Secondary analyses will assess changes in social cognitive variables for each health behavior, over time, by trial group. Mediation analyses [44] will test whether changes in social cognitive variables mediate the effects of the intervention on the targeted health behaviors. Moderation analyses, using ANCOVA, will test whether the intervention is more effective for certain demographic sub-groups (e.g., based on deprivation index scores, ethnicity, etc.) and whether engagement with the intervention moderates the effectiveness of the intervention on health behaviors. Other analysis data sets will be considered as supporting analyses such as the per protocol and the as treated. The above analyses will be repeated for the various secondary outcome measures under consideration (e.g., biochemical markers, health status, academic performance).

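### The single-step .0127 rule is valid, but a Holm-Sidak step-down test would give more power for the second and later behaviours at the same familywise error

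*Protocol article*

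**What the plan says.** The Analysis section defines four primary endpoints: "The primary outcomes will be performance of the four health behaviors (i.e., fruit and vegetable intake, physical activity, alcohol consumption, smoking) at the six-month follow-up". Fruit and vegetable intake, physical activity and alcohol are analysed by ANCOVA adjusted for baseline. Smoking is analysed by logistic regression. The decision rule is "Statistical significance will be declared if any of the primary endpoints are significant at .0127".

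The Sample size calculations section uses the same level, "with a two tailed significance level of .0127", and explains that "the p value has been adjusted to allow for multiplicity in the co-primary endpoints". It states that with 600 per arm "the trial will have at least 80% power to detect a small effect size of *d* = 0.20". Neither section names the adjustment method or the familywise level, and no step-down or other sequential procedure is described.

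**The concern.** A single-step rule holds every endpoint to the strictest threshold, even after another endpoint has already passed. Suppose one behaviour gives p = .009 and a second p = .016. Under the planned rule only the first is declared significant. Holm-Sidak would test the second at .0170 and declare it as well, with the familywise error still held at 5%.

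This matters because each of the four behaviours is a primary outcome, so a reader will want a conclusion on each. The Discussion also contemplates small changes spread over all four behaviours, and that is the setting in which a step-down test gains most.

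**Working it through.** **Inputs from the protocol article.** Four primary endpoints, two-sided .0127 for each, 600 per arm, d = 0.20 (Sample size calculations; Analysis). The Background gives d = 0.16 for online interventions overall, and the Discussion gives d = 0.12 for Internet interventions that target several behaviours.

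**Assumptions.** The familywise level is 5% (inferred below). The correlation between endpoints is not given, so 0, 0.3 and 0.6 are used. No smoking rates are given, so the standardised effect on smoking is set equal to d. Test statistics are treated as normal.

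**Step 1: reproduce the plan's figures.**
- Sidak level for four tests at 5%: 1 − 0.95^(1/4) = .01274, which rounds to .0127. Bonferroni would give .05/4 = .0125, so .0127 points to Sidak.
- Power per endpoint: the noncentrality is 0.20 × √(600/2) = 3.464, and power at .0127 is 83.4% (83.3% with the noncentral t). The claim of at least 80% holds; 556 per arm would suffice for 80%.

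**Step 2: step-down levels.** With m hypotheses still to be tested, the level is 1 − 0.95^(1/m).

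| Order of p value | m | Level | Power for one endpoint at that level, d = 0.20 |
|---|---|---|---|
| Smallest | 4 | .0127 | 83.5% |
| Second | 3 | .0170 | 85.9% |
| Third | 2 | .0253 | 89.0% |
| Largest | 1 | .0500 | 93.4% |

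(The first row uses the unrounded .01274, hence 83.5% rather than 83.4%.) Testing stops at the first non-significant result. No level is below .0127, so every rejection under the planned rule is also a rejection here. The Sidak bound holds for two-sided normal statistics under any correlation, so stepping down adds no independence requirement.

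**Step 3: simulation (400,000 draws, 600 per arm, independent endpoints).** Average power is per truly affected behaviour.

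| True effects | Single-step | Holm-Sidak | At least one endpoint significant, both rules |
|---|---|---|---|
| d = 0.20 on four | 83.5% | about 92% | 99.9% |
| d = 0.20 on three | 83.5% | 88.2% | 99.6% |
| d = 0.20 on two | 83.5% | 85.6% | 97.3% |
| d = 0.20 on one | 83.5% | 83.6% | 84.1% |
| d = 0.16 on four | 61.0% | 71.6% | 97.7% |
| d = 0.12 on four | 33.9% | 39.4% | 80.9% |

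**Step 4: sensitivity to correlation.** With d = 0.20 on all four, average power under Holm-Sidak is 90.9% at correlation 0.3 and 89.8% at 0.6, against 83.5% under the single-step rule in both cases.

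**Step 5: error control.** In every configuration with at least one true null, the simulated familywise error of Holm-Sidak lay between 3.6% and 5.0%. The highest value, .0502, is within simulation error of .05.

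**The case against.** The strongest reply is that nothing here is wrong. The two sections agree with each other, the multiplicity adjustment is declared in advance, and single-step Sidak is a standard, valid choice that delivers the stated power. If the sentence in Analysis is read as one overall verdict on whether any behaviour changed, a step-down test alters nothing, because both rules give the same answer to that question. The single-step rule also yields simple simultaneous confidence intervals for all four effects. All of this stands, and it is why the point is an improvement rather than an error.

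The size of the gain also depends on a truth nobody knows. The Discussion itself warns that participants may take up the material on only one behaviour, and in that case the gain is negligible. That stands too, and the partial-effect and d = 0.12 rows are shown for this reason.

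Three stronger readings are tempting, and the article supports none of them:
- **The trial is underpowered because of this rule.** It is not, on the article's own terms: the 80% claim at d = 0.20 is met.
- **Power to show all four effects is what is being lost.** At d = 0.20 with independent endpoints it would rise from 48.7% to 75.2%, but the article never makes showing all four an objective.
- **A behaviour that narrowly misses .0127 is lost to the cost-effectiveness model.** The Health economic evaluation section models changes in all four risk factors and does not make entry depend on significance.

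What survives the objection is dominance. For conclusions on individual behaviours, the planned rule gives up rejections and gains nothing in familywise error.

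**Conclusion.** The point holds as a loss of efficiency. For the second and later behaviours, the fixed .0127 is uniformly less powerful than Holm-Sidak at the same familywise error. The gain in average power per truly affected behaviour at d = 0.20 is about 8 points if all four respond, about 5 if three do, about 2 if two do and about 0.1 if one does. With d = 0.12 on all four it is about 5 points. Positive correlation between endpoints trims the all-four gain at d = 0.20 to about 6 points at correlation 0.6. Power to show at least one effect is unchanged throughout.

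These figures rest on an inferred 5% familywise level, one test per behaviour, 600 analysed per arm, assumed correlations, and a smoking effect set equal to d. The dominance itself does not depend on the assumed effect sizes or correlations.

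**What to change.** Replace the decision sentence in Analysis with wording such as: the four primary p values will be tested by the Holm-Sidak step-down procedure at a two-sided familywise level of 5%, with levels .0127, .0170, .0253 and .05 from the smallest p value to the largest, stopping at the first non-significant result.

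Keep the sample-size statement at .0127 and describe it as the strictest step, so that the power claim still stands. Naming the method and the familywise level also makes explicit what must now be inferred.

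The cost is one sentence, fixed before outcome data are seen, with no additional participants or data. The trade-off is that simultaneous confidence intervals matching a step-down test are less simple than those of the single-step rule.

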#### Additional analyses

**Randomization check** There will be an exploratory analysis of participants in the two arms of the trial at baseline to ensure that the randomization was successful. Baseline differences between conditions will be controlled for in relevant analyses.

##### Comparison of drop-outs versus completers

In addition, there will be an assessment of differential drop-out rate in the two arms of the trial using survival analysis methods (e.g., Kaplan-Meier plots); additionally, differences between *drop-outs* and *completers* on baseline measures will be assessed.

##### Process evaluation

A process evaluation will be conducted to assess participants’ reactions to the intervention and possible contamination effects. Interviews will be conducted with 20 randomly selected participants from the intervention condition in order to determine the acceptability of, and level of engagement with, the online materials. An online survey at the end of the trial (after the six-month follow-up) with a random selection of 100 control participants will explicitly ask about potential contamination (e.g., did the participant talk to other students about the trial, did they access the *U@Uni* resources, did they change anything they did as a result of finding out about the intervention resources, etc.).

##### Health economic evaluation

The planned health economic analysis will assess the cost-effectiveness of the proposed intervention, balancing the health benefits (in terms of Quality Adjusted Life Years - QALYs) achieved against the costs. Standard approaches to costing the development and implementation of the intervention will be undertaken, separating the fixed costs of set up and implementation from the variable costs per targeted recipient. The full costs of developing the intervention will be estimated as well as the likely costs of adapting the intervention to other universities.

Short-term direct effects on health-related quality of life (as measured by the EQ-5D-3L during the trial) will be compared to intervention costs and short-term health service usage costs in order to estimate the cost per QALY gained within the trial period. Long-term cost-effectiveness modelling will be used to estimate the medium and longer-term impact of changes in behavioral risk-factors (fruit and vegetable intake, physical activity, alcohol consumption and smoking) on costs and QALYs. An integrated model of the consequences of these behavioral risk factor changes on long-term cost and QALY outcomes will be developed based on review of existing models, published literature, and data from the HSE and GLF. The health economic evaluation will consider the extent to which behavior and risk factor changes following the intervention may be sustained or not sustained over the medium and long term.

## Discussion

This paper described (i) an online theory-based intervention (*U@Uni*) that has been designed to promote healthy lifestyle habits in young adults as they make the transition from school to university, and (ii) the randomized controlled trial that will assess its effectiveness.

The intervention has several strengths regarding its timing, delivery and content. First, the intervention capitalizes on the transition from school to university – a significant life change during which health beliefs and behavior may be more malleable. Previous research has indicated that changes in location are important in breaking established habits [7,8] and therefore provide a critical moment to intervene. Moreover, given that over 350,000 students start university each year in the UK, the intervention has the potential to impact on the health behavior habits of a large proportion of young people. Second, the intervention will be delivered using digital technologies, of which young people are the prime users [13,14], thereby ensuring that the intervention is both convenient and engaging to use. Third, the intervention incorporates three complementary behavior change techniques, each of which has a strong theory and evidence base; namely, (i) self-affirmation [15], (ii) theory-based messages [16], and (iii) implementation intentions [17]. A recent meta-analysis reported that online health behavior interventions that were based on theory and used a combination of behavior change techniques produced stronger effect sizes [12].

The proposed research is of theoretical importance as, to date, no studies have examined the efficacy of combining self-affirmation, theory-based messages and implementation intentions to change health behavior. For example, previous studies examining the effects of self-affirmation on health behavior have been limited in the choice of variables to target and the development of the health messages has typically lacked a strong theoretical basis [45]. In addition, while self-affirmation manipulations have been found to lead to positive intentions and initial changes in health behavior, there is limited evidence that they promote sustained behavior change [15]. As a result, additional volitional techniques, such as implementation intentions [25], may be required to support behavior change. In line with this argument, studies have shown that interventions that supplement theory-based health messages with implementation intentions produce larger effects [30-32].

It is likely that the combination of the three behavior change techniques in the online intervention will have a synergistic effect as, together, they address three key factors that may hinder attempts to change health behavior. First, the self-affirmation task will reduce defensive processing and thereby increase engagement with the health messages. Second, the theory-based messages will ensure that the key beliefs underlying each health behavior are targeted. Third, asking participants to form implementation intentions will assist the translation of good intentions into behavior. If the intervention is found to improve students’ health behavior during the first six months of university life, future experimental work may be required to identify the “active ingredients” of the intervention, for example, whether it is necessary to include the self-affirmation manipulation and/or prompt participants to form implementation intentions along with the health messages.

The results of the proposed study will also be of practical importance as the intervention has the potential to improve the health behaviors (and health status) of a large proportion of the population of young people as they enter university. If successful, the intervention could be adapted to other universities in the UK and tested in a cluster RCT. To further test the generalizability of the intervention it may also be applied in other countries where large numbers of young people enter university. However, it should be noted that in many European countries, as well as in Australia and the USA, it is not normative to move away from one’s home city (and one’s home) to go to university, and many students may start university before the legal age for drinking alcohol which may impact on the intervention's suitability. Finally, the intervention could also be adapted and delivered to other school leavers including those who enter the work environment (especially when this involves a move away from the home environment).

The proposed study also has a number of potential limitations. First, there is only a limited time period in which to recruit potential participants as the announcement of ‘A’ level results on which university places in the UK are contingent only happens a few weeks before the start of term. There is also likely to be some attrition over the course of the proposed study. In order to maximize recruitment and retention, a number of strategies that have been identified to increase response rates to online surveys [46] will be used, including non-monetary incentives (i.e., gift vouchers), deadlines for responses, an offer of a summary of the study findings, and a statement that others have responded (in reminder emails).

Second, the time before starting university and the first few months at university are likely to be hectic and stressful for many students which may serve to reduce engagement with the intervention. However, we have taken a number of steps to try to minimize this problem. In particular, the nature of the intervention (i.e., its relevance to the significant life transition) is likely to increase interest in, and engagement with, the intervention. In addition, the use of digital technologies will ensure that the intervention can be easily accessed 24 hours a day. Nonetheless, participants’ engagement with the intervention (e.g., number of times the intervention is accessed) will be measured and its potential moderation of the effectiveness of the intervention will be tested. Furthermore, the introduction of the smartphone application immediately prior to the second semester will hopefully further prompt engagement with the intervention as it coincides with the move back to university after the Christmas vacation and exam period.

Third, given that the trial is being conducted in a single university, there is a possibility of contamination between the intervention and control groups (whereby control participants learn about the intervention and use it themselves). While there are advantages to conducting the trial at a single university (namely, increased control over extraneous factors like the availability of healthy food, opportunities to binge drink, etc.), potential contamination effects will be assessed by conducting a brief online survey at the end of the trial with a random selection of 100 participants in the control group to explicitly ask about potential contamination.

Fourth, the intervention targets multiple health behaviors. Webb et al. (2010) [12] reported that Internet-based interventions that targeted multiple health behaviors tended to report lower effect sizes (*d* = 0.12) than those that targeted single behaviors (*d* = 0.17). The reduced effectiveness of interventions that target multiple health behaviors could be due to a dilution effect (e.g., whereby participants only engage with material for one of the health behaviors) or the effect of compensatory health beliefs (e.g., whereby the performance of an unhealthy behavior such as binge drinking is believed to be negated by performing a healthy behavior such as exercise) [47]. However, should the intervention result in small changes across the four health behaviors, when combined, these changes may still impact on future health outcomes.

